### Study design and setting

The study is designed as a randomized, open-label, multi-center, controlled study in 5 tertiary academic medical centers which are medical, surgical or general ICUs. [name]. W (Shanghai General Hospital, China) will coordinate all the operational processes and [name]. Y (Shanghai Jiao Tong University School of Medicine, China) will conduct all the statistical analyses. Eligible patients who give their consent to participate in the study will be randomly assigned in a 1:1 ratio to treat with rhTPO (rhTPO group) or without any platelet-elevating drugs (control group). Both two groups receive appropriate medical treatment according to the current guideline of Surviving Sepsis Campaign (SSC) [6], and will be assessed for the outcomes at baseline, after the intervention and at 28-day follow-up. The end of the study is defined by the last follow-up of the last enrolled patient.

Patients in rhTPO group will be treated with rhTPO (TPIAO™, Shenyang Sunshine Pharmaceutical Co., Ltd. Shengyang, China) at a dose of 15000u/d, subcutaneous injection, for 7 consecutive days. RhTPO in the study is for free. The time from randomization to administration of rhTPO will be within 24 h. The drug will be terminated when PCs reach the standard of clinical recovery of platelets (PCs ≥100 × 10^9^/L or the increasing of PCs ≥ 50 × 10^9^/L lasting for at least 3 days) or severe adverse effects happened. The clinical recovery time of platelets was defined as the time it takes to reach clinical recovery. Patients in control group will not be treated with any platelet-elevating drugs.

In both control and rhTPO groups, there is the same standard of platelet transfusion: when PCs are below 10 × 10^9^/L in the absence of apparent bleeding; or below 20 × 10^9^/L if the patient has a significant risk of bleeding; or below 50 × 10^9^/L if the patient has active bleeding or need invasive operation. During the study, any other platelet-elevating drugs will be forbidden.

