### Sample size

The 28-day all-cause mortality of sepsis patients varies in different patient populations. According to the previous studies, the 28-day mortality of sepsis patients with severe thrombocytopenia was more than 50% [19, 20, 31]. Furthermore, in our single-center, retrospective, cohort study, the 28-day mortality of these patients treated with rhTPO was 29.2%. Our sample size was calculated to detect a 20% difference (rhTPO group 30% Vs Control group 50%) in 28-day mortality. Based on a two-tailed test of two independent means, with a significance (α) level of 0.05 and 80% power, a minimum of 91 patients in each group for a total sample of 182 patients was required. It was assumed that the loss rate of this study is no more than 10%, and the minimum sample of this study was 100 patients in each group for a total sample of 200 patients.

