#### Secondary outcomes

Secondary outcomes of this study have been seen as follow: 1) The changes of platelets counts (PCs) in the first 7 days; 2) The clinical recovery time of PCs; 3) The amount and proportion of blood transfusion (including platelets, RBC, Frozen plasma); 4) The changes of biomarkers of infection including procalcitonin, C-reactive protein (CRP), endotoxin; 5) The changes of the markers of organ function including cardiac, hepatic, renal, coagulation function; 6) The days free from advanced organ support (including vasoactive drugs/mechanical ventilation/renal replacement therapy) at 28 days; 7) The incidence of bleeding event; 8) The incidences of drug-related adverse events; 9) The length of ICU and hospital stay.

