### Statistical methods

Analyses will be conducted on an intention-to-treat and per-protocol population basis. Data for each assessment will be summarized for each treatment group and the descriptive statistics will be calculated depending on the data distribution for each assessment. Outcomes will be collected at the times defined in the study protocol. The primary efficacy variable will be the change in 28-day mortality. The change in 28-day mortality between the two groups will be analyzed by using Chi-Square. The proportions will be analyzed using logistic regression including baseline as covariate and group as a fixed factor. The comparisons among continuous parametric data were conducted by using t-test or Anova analysis, whereas the A Mann-Whitney U test or a Kruskal-Wallis test were used to analyze continuous nonparametric data. Comparisons between enumeration data ware conducted by Chi-Square or Fisher exact method. Survival comparison between groups was analyzed by using Log-rank analysis. *P* < 0.05 was considered to indicate statistical significance.

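### Continuous change outcomes are compared by unadjusted tests although baseline values are collected; baseline adjustment would be as precise or more so, mainly for the biomarkers and organ-function markers

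*Protocol article*

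**What the plan says.** All references are to the protocol article.

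- **Statistical methods, continuous data:** "The comparisons among continuous parametric data were conducted by using t-test or Anova analysis". Nonparametric data get Mann-Whitney or Kruskal-Wallis tests. No covariate is mentioned for either.
- **Statistical methods, proportions:** "The proportions will be analyzed using logistic regression including baseline as covariate and group as a fixed factor". This is the only baseline covariate in the section, and the term is not defined.
- **Secondary outcomes:** item 1 is the change in platelet count over the first 7 days, item 4 is "The changes of biomarkers of infection including procalcitonin, C-reactive protein (CRP), endotoxin", and item 5 is the change in cardiac, hepatic, renal and coagulation markers.
- **Data collection:** baseline laboratory results, including organ-function and infection markers, are taken within 24 h after randomisation. When there are several measurements on one day, the worst is kept.
- **Study design and setting:** the first rhTPO dose may be given at any time in the same 24 h.

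**The concern.** Outcomes 4 and 5, and to a lesser extent outcome 1, are changes from a value that the trial already measures. The named tests cannot use that value as a covariate. A t-test on the change subtracts the whole baseline, whatever the true regression slope on it. A t-test on the follow-up value ignores it. Either way, some precision may be lost and some chance imbalance in the marker left in the comparison. Randomisation balances SOFA and APACHE II, and only after forty patients (Randomization section); it does not balance the markers themselves. What is at stake is the width of the intervals on these secondary outcomes.

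**Working it through.** **The plan's own figure.** The Sample size section reads "Our sample size was calculated to detect a 20% difference (rhTPO group 30% Vs Control group 50%) in 28-day mortality", "with a significance (α) level of 0.05 and 80% power", two-tailed. With the unpooled normal approximation, n per arm = (0.30×0.70 + 0.50×0.50) × (1.960 + 0.842)² / 0.20² = 90.3, so 91. This matches "a minimum of 91 patients in each group for a total sample of 182 patients was required". That sample size is not in question; 91 per arm is used below only as a reference size.

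**Formulas.** Let ρ be the correlation between baseline and follow-up, and k the baseline SD divided by the follow-up SD. In units of the follow-up variance, the large-sample variances of the treatment effect are proportional to:

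- t-test on the change: 1 + k² − 2ρk
- t-test on the follow-up value: 1
- ANCOVA on baseline: 1 − ρ²

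Change score minus ANCOVA is (k − ρ)², and follow-up value minus ANCOVA is ρ². Neither is ever negative. The loss from the change score vanishes only when k = ρ.

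**Equal SDs (k = 1).** The ratio of ANCOVA to change-score variance is (1 − ρ²)/(2(1 − ρ)) = (1 + ρ)/2. The document gives neither ρ nor any SD, so ρ is assumed. The power columns also assume an effect of 0.4 follow-up SD with 91 per arm.

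| ρ | Change score | ANCOVA | Ratio | Power, change / ANCOVA | n per arm for 80% power, change / ANCOVA |
|---|---|---|---|---|---|
| 0.3 | 1.40 | 0.91 | 0.65 | 62.6% / 80.7% | 138 / 90 |
| 0.5 | 1.00 | 0.75 | 0.75 | 77.0% / 87.6% | 99 / 74 |
| 0.7 | 0.60 | 0.51 | 0.85 | 93.6% / 96.5% | 59 / 51 |

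A simulation of 4,000 runs at ρ = 0.5 gave 76.5% and 86.7%, in line with the table. If the follow-up value is tested instead of the change, the ratio is 1 − ρ²: 0.91, 0.75 and 0.51.

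**Narrow baseline spread (k = 0.3, assumed).** This is plausible for platelets: entry is capped below 50 × 10^9/L (Study population), while recovery means at least 100 × 10^9/L or a rise of at least 50 × 10^9/L (Study design and setting).

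- ρ = 0.1: 0.99/1.03 = 0.96
- ρ = 0.3: 0.91/0.91 = 1.00 (simulated power 80.1% for both)
- ρ = 0.5: 0.75/0.79 = 0.95
- ρ = 0.7: 0.51/0.67 = 0.76

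**Wide baseline spread (k = 1.5, assumed).** The ratio is 0.39, 0.43 and 0.44 for ρ = 0.3, 0.5 and 0.7. The size therefore depends on k as much as on ρ.

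**Limits.** The formulas compare t-tests with ANCOVA on the same scale. They do not directly cover the rank tests, for which the natural comparison is ANCOVA on a log or rank scale. The power figures assume that every patient has a follow-up value. With planned 28-day mortality of 30% and 50%, 91 per arm would leave about 64 and 46 alive at day 28 (91×0.70 and 91×0.50), so absolute power at late days would be lower.

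**The case against.** The strongest reply is that nothing here is invalid. Under randomisation a t-test on the change is unbiased and already uses baseline by subtraction. The choice of model for a secondary outcome is often left to the analysis plan. All of that is true. But this document does name the tests, and a plan that used ANCOVA would depart from them, so the improvement is worth making here.

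Three stronger readings are tempting, and the document does not support them.

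- **That adjustment is wrongly given to mortality.** A reader might argue that everyone is alive at randomisation, so mortality has no baseline. But baseline in the logistic model may well mean severity: the Randomization section names SOFA and APACHE II as balancing factors, and adjusting a proportion for them is sensible. The fault is an undefined term.
- **That the arms are assessed at different times.** The overview says patients "will be assessed for the outcomes at baseline, after the intervention and at 28-day follow-up". Since controls have no intervention and rhTPO can stop early, a reader might infer, say, a day 4 against day 7 mismatch. Nothing says that stopping the drug moves a laboratory assessment. Platelets have a 7-day window, Data collection refers to time points set by the protocol for all patients, and a condensed article may leave the schedule to the full protocol.
- **That 15% to 35% of the sample is wasted on all three outcomes.** That range needs equal SDs, which is least plausible for platelets.

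**Conclusion.** The point stands as an improvement to the analysis of secondary outcomes. For the infection biomarkers and organ-function markers, adjusting for the marker's baseline could reduce the variance to about 0.65 to 0.85 of that of a change-score t-test, if SDs are equal and ρ lies between 0.3 and 0.7. For platelets the ratio may be 0.95 to 1.00 (k = 0.3, ρ from 0.1 to 0.5), so little or no gain should be promised there. Both ranges rest on assumed correlations and SD ratios. What does not depend on them is the direction: in large samples neither t-test beats ANCOVA on the same scale. The 28-day mortality test and the total of 200 patients are unaffected.

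**What to change.** - **Model.** Analyse outcomes 1, 4 and 5 by ANCOVA or a repeated-measures model with the marker's own baseline value, SOFA and APACHE II as covariates. Use a log scale for skewed markers. Compare both arms at the same protocol days since randomisation.
- **Baseline value.** Use the last value before the first rhTPO dose, and the enrolment value in controls. The present rules allow baseline up to 24 h after randomisation and keep the worst value of the day, so a recorded baseline could follow the first dose. Platelets are necessarily counted at screening; for procalcitonin, CRP and endotoxin the document shows no value before randomisation.
- **Death.** State that marker comparisons are among patients alive on that day, with the limits this puts on interpretation, or handle death explicitly. A repeated-measures model should not silently extrapolate markers beyond death.
- **Logistic model.** Define baseline as SOFA and APACHE II.

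The cost is small but goes beyond wording: slightly more analysis work, and a pre-dose sample must be identified for each treated patient. No change in sample size is needed.

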### Data collection

A case report form (CRF) will be used for all patient who met the enrollment criteria to collect the data. Patients will be followed up to 28 days after randomization. The data will be abstracted from the patients’ electronic medical records: age, ethnicity, gender, patients’ type (medical/surgical), co-comorbidities, sites and pathogens of infection. Then, clinical characteristic baseline and laboratory results were tested within the first 24 h after randomization, including markers of organ functions and biomarkers of infection (Procalcitonin, C-reactive protein, Endotoxin). The severity of disease scores will be recorded, including APACHE II, SOFA, and DIC scores [32] in the first 24 h. The basic serum TPO level in patients will be tested by ELISA Kit (R&D Systems, Minneapolis, MN, USA). The clinical data will be tested in the point-in-time followed by protocols on the day of enrollment and periodically thereafter until the time of discharge or death, including the numbers of blood products transfusion (including platelets), antibiotics, concomitant medication, days free from advanced organ support, adverse events and the length of ICU or hospital stay. And if several clinical data or measurements will be performed at one day, the lowest/worst data will be retained. Patient status (survive or death) at the 28 days will be recorded through chart review or contact patients if necessary, and the major causes of death will be recorded if the patients will be died. Flowchart of this study procedure can be seen in Fig. 1.

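### The rule for continuous data does not suit platelet recovery time or ICU/hospital stay when 50% versus 30% of patients are planned to die; it can bias both against the better-surviving arm

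*Protocol article*

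**What the plan says.** All references are to the protocol article.

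- **Statistical methods** assigns tests by type of data, not by outcome. Continuous data go to a t-test or ANOVA if parametric, "whereas the A Mann-Whitney U test or a Kruskal-Wallis test were used to analyze continuous nonparametric data". Log-rank is the only time-to-event method, and its sentence concerns the survival comparison. Analyses are on intention-to-treat and per-protocol populations.
- **Study design and setting**: "The clinical recovery time of platelets was defined as the time it takes to reach clinical recovery". This gives no value to a patient who dies or never recovers.
- **Secondary outcomes** lists recovery time (item 2), days free from advanced organ support at 28 days (item 6) and "The length of ICU and hospital stay" (item 9).
- **Sample size** plans on 28-day mortality of "rhTPO group 30% Vs Control group 50" percent.
- **Data collection**: "Patients will be followed up to 28 days after randomization". It also says that clinical data, length of stay included, are collected periodically until discharge or death.
- **Objectives** names a shorter platelet recovery time among the trial's aims.

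**The concern.** Recovery time and length of stay are both interrupted by death. A patient who dies on day 3 has no recovery time, and has a 3-day stay only in the sense that death ended it. A t-test or Mann-Whitney test needs one number per patient, so the analyst must do one of two things:

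- **Leave out the deaths.** The test then compares groups selected by something that happened after randomisation. With 50% and 30% mortality, about 50 of 100 control patients and 70 of 100 rhTPO patients would remain. That is no longer the randomised comparison the intention-to-treat statement promises.
- **Count time up to death.** A quick death then scores as a short stay, which favours the arm with more early deaths.

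Faster platelet recovery is a stated objective, so a main secondary claim rests on this analysis. The trial is open-label, so a rule for deaths chosen after the data are seen would be open to challenge.

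**Working it through.** **1. The plan's own figure.** Mortality 0.50 versus 0.30, two-sided alpha 0.05, power 80%. The unpooled two-proportion formula gives

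n = (1.960 + 0.842)² × (0.50×0.50 + 0.30×0.70) / 0.20² = 7.85 × 0.46 / 0.04 = 90.3, so 91 per arm.

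This agrees with "a minimum of 91 patients in each group for a total sample of 182 patients was required". The mortality figures used below are therefore the plan's own, with 100 patients per arm.

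**2. Assumptions not in the documents.** Stay in survivors is lognormal with median 14 days and log-SD 0.6 in both arms. Times of death are exponential with mean 8 days, capped at 28. The daily platelet recovery hazard is 0.10 in both arms. The drug thus changes mortality only.

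**3. Stay counted to death or discharge.** With mortality p, the proportion with stay up to x days is

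F(x) = (1 − p) × Φ(ln(x/14)/0.6) + p × (1 − exp(−x/8)).

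- Control, x = 10.0: 0.5 × 0.287 + 0.5 × 0.713 = 0.500.
- rhTPO, x = 11.8: 0.7 × 0.388 + 0.3 × 0.771 = 0.503.

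The medians are therefore about 10.0 and 11.8 days (11.7 if the second equation is solved exactly), although survivors' stay is the same in both arms. In simulation Mann-Whitney gives p < 0.05 in about 30% of trials, almost always with rhTPO longer. Restricted to survivors, it rejects in about 5%.

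**4. Recovery time in recoverers only.**

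- Survivors: recovery by day 28 has probability 1 − exp(−2.8) = 0.939. The mean time among those who recover is 10 − 28 × 0.0608/0.939 = 8.19 days.
- Patients who die: recovery before death has probability 0.10/(0.10 + 0.125) = 0.444, with mean time 1/0.225 = 4.44 days. (The cap at 28 days is ignored here.)
- Control: (0.5×0.939×8.19 + 0.5×0.444×4.44)/(0.5×0.939 + 0.5×0.444) = 4.83/0.692 = 7.0 days.
- rhTPO: (0.7×0.939×8.19 + 0.3×0.444×4.44)/(0.7×0.939 + 0.3×0.444) = 5.98/0.791 = 7.6 days.

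Mann-Whitney rejects in about 7-9% of simulated trials, against a nominal 5%. The denominators show what is lost. In all randomised patients, 69% of the control arm and 79% of the rhTPO arm recover by day 28, yet the recoverer-only mean makes rhTPO look slower.

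**5. Sensitivity to the assumptions.** A second simulation used lognormal latent times (median stay 14 days, recovery 7 days), earlier or later deaths, and death either independent of severity or related to it. With the drug changing mortality only, rhTPO minus control was:

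| Outcome and handling of death | Mean difference (days) | rhTPO significantly longer or slower |
|---|---|---|
| Stay, counted to death | +2.0 to +2.8 | 39-58% of trials |
| Stay, survivors only | about 0 (death unrelated to severity) to +0.9 (related) | 2-7% |
| Recovery time, cut off at death | +0.7 to +1.2 | 19-36% |
| Recovery time, recoverers only | +0.2 to +0.7 | 5-12% |

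If the drug also speeds recovery by a factor of 1.2, the recovery-time difference becomes −0.9 to −0.4 days in recoverers, or −0.3 to +0.1 days cut off at death.

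**6. Organ-support-free days.** In the same simulation, scoring death as 0 gives +3.5 to +3.7 days in favour of rhTPO when only mortality differs. Counting 28 minus days of support and ignoring death gives −0.9 to −1.3 days. The protocol states neither rule.

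**The case against.** The strongest reply is that the protocol names no test for these outcomes. It gives generic rules by data type, and a fuller protocol or an SAP may say how deaths enter. That stands as a limit on confidence, and detail left to such a document is not the fault here. What remains is that the stated rule itself does not fit: outcomes in days fall under the continuous-data tests, and the one time-to-event method is tied to survival. An SAP that followed the rule as written would carry the problem forward.

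A second reply is that the size depends on an unstated choice. This is correct. The 30% figure arises only if stay is counted to death; in survivors only, with death unrelated to severity, the test keeps its 5% level. But survivor-only analysis gives up the randomised comparison, so neither choice is sound.

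A reader might infer several stronger claims that the documents do not support:

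- *That rhTPO will look slower and longer.* It can, but a true effect on recovery of modest size is enough to offset or reverse the bias in recovery time.
- *That organ-support-free days suffer the same fault.* With death scored 0, the comparison favours the better-surviving arm, and the rank test already allowed is suitable.
- *That stays are censored at day 28.* Follow-up is to 28 days, but the Data collection section also speaks of collection until discharge or death, so this is not established.
- *That platelet recovery can certainly be analysed to day 28.* Platelet changes are listed for the first 7 days, and the article gives no later sampling schedule beyond periodic collection.

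**Conclusion.** The concern holds for length of stay and, to a smaller degree, for platelet recovery time. The continuous-data rule is unsuited to outcomes that death cuts short when mortality is planned to differ by 20 percentage points, and it can bias them against the arm with better survival. Under the assumptions of steps 2 to 4, the false difference in median stay is about 1.8 days (10.0 versus 11.8), significant in about 30% of trials. For recovery time among recoverers it is about 0.6 days (7.0 versus 7.6), with about 7-9% rejection.

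Only the mortality rates and the sample size come from the protocol. The distributions of stay, death and recovery times are assumed, and the results move with them. These are secondary outcomes; the 28-day mortality analysis is not touched. The change should be made, but the trial's main result does not depend on it.

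**What to change.** Replace the generic rule for these two outcomes, in all randomised patients:

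- **Platelet recovery**: time to clinical recovery with death as a competing event, over the period in which platelet counts are actually collected. Report cumulative incidence by arm, Gray's test and the cause-specific hazard ratio. Both measures are needed, because a drug that only prevents deaths raises the cumulative incidence of recovery while leaving the cause-specific hazard ratio at 1.
- **ICU and hospital stay**: time to discharge alive, with death competing.
- **Survivor-only and recoverer-only summaries**: descriptive, without a test.
- **Organ-support-free days**: state the score for death (for example 0) and keep the rank test.

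The cost is analysis wording, fixed before the data are examined. Discharge and death are already recorded. The sampling period for platelet counts should be confirmed before a time horizon for recovery is set. The small downside is that results appear as cumulative incidences rather than mean days.

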## Discussion

It has been confirmed that sepsis patients with severe thrombocytopenia have the higher mortality and the longer the duration of thrombocytopenia lasts, the worse the prognosis of these patients have. Platelets maybe a novel target to improve the prognosis of sepsis patients with severe thrombocytopenia. To date, there are three main platelet-elevating drugs in clinical practice, which are recombinant human interleukin-11(rhIL-11), thrombopoietin receptor agonist (TPO-RA) and rhTPO.

RhIL-11 is produced by recombinant DNA technology in *Escherichia coli*, which has shown effects on multiple hematopoietic cell types. And rhIL-11 could induce megakaryocyte maturation and stimulate megakaryocyte to increase PCs. In addition, rhIL-11 was involved in regulating the activity of non-hematopoietic cells, including regulating the growth of intestinal epithelial cells, osteoclast proliferation, host response and releasing inflammatory factors [33]. In hematological tumors patients with chemotherapy-induced thrombocytopenia, rhIL-11 could rapidly increase PCs, significantly reduce the incidence of bloodstream infection and improve the prognosis [34]. Recently, Wan B et al. reported that rhIL-11 could promote the recovery of PCs, reduce the expression of TNF-alpha and IL-6, alleviate inflammatory response, thus reducing the mortality of patients with thrombocytopenia [35]. However, rhIL-11 cannot increase the number of megakaryocytes and its clinical effect is relatively slow. Moreover, rhIL-11 itself is an inflammatory factor and has many adverse effects (including water and sodium retention, tissue edema, pleural effusion, acute pulmonary edema, arrhythmia), which limit the clinical application of rhIL-11 in sepsis. TPO-RAs (including eltrombopag or romiplostim) are another novel platelet-elevating drugs that bind to and activate the thrombopoietin (TPO) receptor, induce megakaryocyte progenitor proliferation by JAK2/STAT5 pathway, and finally increase PCs in chronic thrombocytopenia induced by immune, HCV infection or cirrhosis [36–38]. Until now, there is no report about TPO-RAs in sepsis treatment.

RhTPO specifically acts on the hematopoietic regulatory factors of megakaryocyte and promotes all stages of megakaryocyte formation. The drug is approved by the China State Food and Drug Administration for the treatment in patients with chronic immune or chemotherapy-related thrombocytopenia refractory to first-line therapy and no severe adverse effect has been reported. For sepsis, a retrospective study in elderly sepsis patients with thrombocytopenia reported that rhTPO increased PCs, reduced bleeding events, recovered organ function [39]. And rhTPO could rapidly restore PCs in 76.32% of patients with thrombocytopenia within 5 days, reduce the number of platelet transfusion and 28-day mortality in perioperative patients with abdominal infection [40]. However, there are the limitations in these two trials: 1) sepsis patients both were diagnosed by sepsis-1.0 standard; 2) PCs of whom was less than 100 × 10^9^/L; 3) the sample sizes were small and both of them were single-center non-randomized studies. The questions about the patients’ selecting, timing, effect and safety of rhTPO in sepsis are still unclear. Therefore, further studies in this field need to be explored, especially multi-center RCT studies.

In conclusion, RESCUE trial only focuses on sepsis patients with severe thrombocytopenia (PCs < 50 × 10^9^/L) and sepsis-3.0 standard will be used to diagnose which has the higher sensitivity than the other sepsis standards. To our knowledge, it is the first RCT study to explore the impact of rhTPO for severe thrombocytopenia in sepsis patients diagnosed by sepsis-3.0 standard. Furthermore, if the hypotheses are confirmed, RESCUE trial results will be of significant clinical value on the targeted therapy for sepsis patients with severe thrombocytopenia, and rhTPO probably becomes an effective rescue treatment for these sepsis patients except for platelet transfusion.

